#### Criteria for discontinuing or modifying allocated intervention {11b}

Given that the procedures in this study are generally low risk, the likelihood of participants’ withdrawal or discontinuation is minimal. However, since the participants are older adults with chronic diseases, the chance of dropping out due to sudden health deterioration is still possible. The participants will be able to discontinue the intervention sessions at any point at their request.

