#### Sample size {14}

The required sample size is estimated for one of the primary outcomes, i.e. patient activation. With reference to previous studies of patient activation interventions on chronic disease self-management [43, 61], the sample size is estimated on the basis of an effect size *f* = 0.2. Using G*Power, power analyses revealed that a total sample size of 266 is required to detect differences amongst the two intervention conditions (i.e. health coaching delivered by lay health workers vs. health professionals), using a multivariate analysis of variance with an effect size of 0.2, a power of 90% and an alpha level of 0.05, with 133 individuals in each condition. Considering the dropout rate of 30% over a period of three months, the target sample size is adjusted to 380 (with 190 individuals in each condition).

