## Statistical methods

### Statistical methods for primary and secondary outcomes {20a}

Descriptive statistics will be used to summarise participants’ baseline demographics and outcome variables throughout the study time points. Attrition analysis and randomisation tests will be carried out to test for differences in demographic and outcome variables between the intervention and comparison groups. Repeated measures ANCOVA will be conducted to examine any significant improvements in the primary and secondary outcomes across baseline and 3-month follow-up assessments whilst controlling for the effects of demographics (i.e. age, sex, education, chronic diseases) and the frequency of intervention sessions. Generalised estimating equation (GEE) analyses will be conducted to compare the primary and secondary outcomes at the 3-month follow-up between the intervention and comparison groups whilst controlling for the effects of demographics and the frequency of intervention sessions. The intention-to-treat principle will be adopted in the analyses for all the primary and secondary outcomes by imputing missing follow-up outcome data with their baseline values (i.e. assuming no change after the intervention for the primary and secondary outcomes) under the assumption of data being missing not at random. This assumption is plausible in the sense that missing data because of dropouts or non-responses are more likely amongst old-old participants with severe health problems. All statistical analyses will be conducted using R software. The treatment effect within and between the two groups will be assessed using Cohen’s *d* statistic [64].

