### Methods for additional analyses (e.g. subgroup analyses) {20b}

To evaluate the robustness of the analysis results, sensitivity analyses for the primary and secondary outcomes will be conducted under the assumptions that data are missing completely at random (MCAR) and data are missing at random (MAR). Complete case analyses will be conducted for the primary and secondary outcomes. The results are expected to be unbiased under the MCAR condition. Little’s MCAR test will be used to justify the plausibility of the assumption. In addition, if the assumption of MCAR is not supported, the sensitivity analyses will be conducted on the basis of multiple imputations under the assumption of MAR. A subgroup analysis will be conducted to explore any interaction effects.

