### Methods in analysis to handle protocol non-adherence and any statistical methods to handle missing data {20c}

Intention-to-treat analysis will be used to minimise the impact of participant dropouts and non-adherence to the protocol by analysing all participants according to their original assignment, regardless of whether they completed the study. Missing data will be imputed using statistical methods to ensure that the analysis is not biased by missing data.

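### Primary carry-forward of baseline values shrinks the between-arm difference by the dropout fraction when dropout is similar in both arms, which favours the hypothesised comparability, and the stated 90% power was not computed for that analysis

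*Protocol article*

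**What the plan says.** Statistical methods {20a} sets the rule: intention-to-treat for all primary and secondary outcomes, achieved by "imputing missing follow-up outcome data with their baseline values". It spells this out as no change after the intervention and labels the assumption missing not at random (MNAR). The reason given is that dropout and non-response are likelier among very old participants with severe health problems. The arms are compared on the 3-month outcomes by GEE. The listed covariates are demographics and session frequency; the baseline outcome is not among them.

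Sample size {14} plans "with an effect size of 0.2, a power of 90% and an alpha level of 0.05", which gives 266 participants, and then: "Considering the dropout rate of 30% over a period of three months, the target sample size is adjusted to 380".

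Additional analyses {20b} plans complete-case analyses as sensitivity analyses in any case. Multiple imputation is conditional: "if the assumption of MCAR is not supported, the sensitivity analyses will be conducted on the basis of multiple imputations". Little's test is to inform that judgement. Section {20c} states the aim: "Missing data will be imputed using statistical methods to ensure that the analysis is not biased by missing data".

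Objectives {7} hypothesises that both arms improve and that improvement with lay coaches is comparable to that with professionals.

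**The concern.** Filling a missing follow-up value with the baseline value fixes that person's change at exactly zero, in either arm. Any difference between arms is then diluted by the proportion missing. In a trial meant to show superiority that is often called conservative. Here the hoped-for result is comparability, so dilution works in its favour.

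Three further points follow.

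- The rule is a single deterministic imputation, so the analysis carries no uncertainty for values nobody measured.
- The rationale concerns who is likely to drop out. It says nothing that makes zero change the likely outcome for them. Missingness that depends on age and disease burden, which are at least partly recorded at baseline (age and number of chronic diseases are stratification factors), fits a missing-at-random (MAR) mechanism. Severe illness fits worsening at least as well as stability.
- The power calculation removes the dropouts, while the primary analysis keeps them with zero change. The two describe different analyses.

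At stake is the main conclusion for every primary outcome: a real deficit with lay coaches could look smaller than it is, or a difference in retention could look like a difference in effect.

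**Working it through.** **Inputs.** From Sample size {14}: f = 0.2, power 90%, alpha 0.05, 266 evaluable (133 per arm), 30% dropout, 380 randomised (190 per arm). For two equal groups d = 2f = 0.4 SD. Assumed, because the document gives no figure: baseline/follow-up correlation r, dropout by arm, and any non-inferiority margin.

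**1. The plan's own figures.** A two-group F test on one outcome with f = 0.2 has power 90.15% at N = 266. Normal approximation: SE = √(2/133) = 0.1226; Φ(0.4/0.1226 − 1.96) = 0.904. Inflation: 266/0.7 = 380. Both figures reproduce, with the 30% counted as lost.

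**2. Shrinkage, equal dropout.** Expected difference = 0.40 × (1 − 0.30) = 0.28 SD. Simulated estimates averaged 0.28 in every scenario with 30% dropout in both arms.

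**3. Power, 3-month score, no baseline outcome covariate, SD unchanged.** SE = √(2/190) = 0.1026; Φ(0.28/0.1026 − 1.96) = Φ(0.769) = 0.779 (exact F 77.7%). At 10%, 20% and 40% dropout it is 93.9%, 87.7% and 64.8%. Restoring 90% at 30% dropout would need 2 × (1.96 + 1.2816)²/0.28², rounded up to 269 per arm.

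**4. Power if the GEE uses baseline.** Simulation with 190 per arm, random 30% dropout and a true difference of 0.4 raw SD. Ranges cover mean improvements of 0.4 vs 0, 0.6 vs 0.2 and 0.8 vs 0.4 SD.

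| Analysis | r = 0.3 | r = 0.5 | r = 0.7 |
|---|---|---|---|
| Carry-forward, 3-month score | 74–77% | 75–78% | 74–78% |
| Carry-forward, change score | 75–79% | 87–90% | 97–99% |
| Carry-forward, baseline-adjusted | 84–89% | 92–95% | 98–99% |
| Completers, 3-month score | 90–91% | 90–91% | 90–91% |
| Completers, change score | 79% | 90% | 98–99% |
| Completers, baseline-adjusted | 92–93% | 96% | above 99% |

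If f = 0.2 is read in SD units of change, carry-forward power is 87–90%, because zero-change cases shrink the SD as well as the mean.

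**5. Unequal dropout.** Equal true benefit of 0.4 SD, assumed dropout 20% vs 40%: 0.4 × (0.8 − 0.6) = 0.08 SD spurious difference. Simulated type I error (r = 0.5) was about 13–18%, depending on the model, against 5%. Swapping the arms reverses the sign.

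**6. Illustrative non-inferiority error.** The protocol gives no margin M. If one were tested at one-sided 2.5% with a true deficit equal to M, the false-claim rate would be P(Z > 1.96 − 0.3M/0.1026): 21% for an assumed M = 0.4 SD and 14% for M = 0.3 SD, without baseline adjustment.

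**7. The gate.** A non-significant Little's test does not establish that data are missing completely at random (MCAR). Under {20b}, such a result leaves only carry-forward and complete cases. Neither lets dropouts worsen, although the primary assumption is labelled MNAR.

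**The case against.** The strongest reply has four parts.

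*Power.* The 78% is conditional. {20a} names GEE, which can use both time points, and does not give the model terms. With change scores, power under carry-forward is close to that of the matching completers' analysis; with baseline adjustment it can exceed 90%. This stands. A reader might infer that the trial simply has 78% power, but the document supports that only for the follow-up-only comparison.

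*The rationale.* A reader might infer that the protocol contradicts itself, because {11b} says "the chance of dropping out due to sudden health deterioration is still possible" while {20a} imputes no change. The documents do not support that. {11b} concerns stopping intervention sessions and calls withdrawal unlikely, and {20a} never says that dropouts' scores fall. The rationale is weak, not self-contradictory.

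*Visibility.* A reader might infer that no better analysis will be run. Complete-case analysis is unconditional. If the covariates in {20a} are carried into it, it is approximately unbiased when dropout depends on them. The distortion would therefore probably show, but only as a sensitivity result; the primary result stays as it is.

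*Truth of the assumption.* If dropouts really gain nothing, 0.28 SD is the real intention-to-treat difference and a MAR analysis overstates it. This is fair, and is the reason to retain carry-forward as a sensitivity analysis. It does not justify making it primary on the reason given.

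**Conclusion.** The point holds. The primary rule is stated in the protocol itself, so it is not a detail left to an analysis plan. At the planned 30% dropout, similar in both arms, it shrinks the difference among would-be completers by 30%, towards the hypothesised comparability. That shrinkage does not depend on how the GEE is specified. If dropout differs by arm, the bias can take either sign, so convergence of the arms is not assured.

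The stated 90% power does not describe the planned analysis of 380. It is about 78% for the comparison as {20a} describes it. With change scores or baseline adjustment it runs from about 79% (a few points lower if both arms improve and r is low) to above 90%.

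The 21% and 14% false-claim rates are illustrations on assumed margins. Baseline adjustment at an assumed r = 0.6 would give 38% and 24%, but a reader should not set these beside the 78%: in that model power is about 97%.

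**What to change.** - Make multiple imputation or a likelihood-based model under MAR the primary analysis, including the baseline outcome and the stratification covariates (age, sex, education, number of chronic diseases).
- Run it unconditionally and remove Little's test as a gate.
- Keep carry-forward of baseline as a sensitivity analysis, and add an MNAR sensitivity analysis in which dropouts may worsen.
- If carry-forward stays primary, restate the power for that analysis: about 78% for the follow-up-only comparison, or the figure for a baseline-using model with its assumed correlation stated.

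The cost is revised wording and a little more programming in R. No new data are needed. The downside is that a MAR estimate overstates the difference if dropouts truly gain nothing; the retained carry-forward analysis would show that.

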### Interim analyses {21b}

Not applicable. No interim analysis will be conducted because the adverse effects of participation for participants are minimal in this study.

### Methods for additional analyses (e.g. subgroup analyses) {20b}

To evaluate the robustness of the analysis results, sensitivity analyses for the primary and secondary outcomes will be conducted under the assumptions that data are missing completely at random (MCAR) and data are missing at random (MAR). Complete case analyses will be conducted for the primary and secondary outcomes. The results are expected to be unbiased under the MCAR condition. Little’s MCAR test will be used to justify the plausibility of the assumption. In addition, if the assumption of MCAR is not supported, the sensitivity analyses will be conducted on the basis of multiple imputations under the assumption of MAR. A subgroup analysis will be conducted to explore any interaction effects.

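### Multiple imputation under MAR depends on MCAR being found unsupported, with Little's test the only named check; it should be run and reported whatever that test shows

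*Protocol article*

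**What the plan says.** **Primary handling.** In the protocol article, section {20a} (statistical methods for primary and secondary outcomes), missing follow-up values are replaced by the participant's own baseline value, "under the assumption of data being missing not at random". The reason given is that dropout and non-response are likelier among the oldest participants with severe health problems.

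**Sensitivity analyses.** Section {20b} (methods for additional analyses) first names two assumptions, MCAR and MAR. It then sets out:

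- Complete cases, without condition: "Complete case analyses will be conducted for the primary and secondary outcomes. The results are expected to be unbiased under the MCAR condition".
- A check on that assumption: Little's "MCAR test will be used to justify the plausibility of the assumption".
- Imputation under MAR, with a condition: "if the assumption of MCAR is not supported, the sensitivity analyses will be conducted on the basis of multiple imputations".

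No significance level or variable list is given for the test. Section {20c} says only that missing data will be imputed by statistical methods and names none.

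**The concern.** The opening sentence of {20b} plans an MAR analysis. The later sentence makes it depend on MCAR being found unsupported. Read as written, a non-significant Little's test leaves two sets of results: baseline carried forward, and complete cases.

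That rule treats failure to reject as support for MCAR. The test can miss a modest difference between dropouts and completers. It also compares missingness patterns pooled over arms, so dropout that runs in opposite directions in the two arms can cancel out. The protocol's own account of who drops out already speaks against MCAR.

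At stake is the quality of the check on a single-value imputation applied to an expected 30% of participants, in a trial whose question is whether two types of coach give comparable results.

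**Working it through.** **1. The plan's own figures (sample size section {14}).** Stated: f = 0.2, power 90%, alpha 0.05, total 266, dropout 30%, target 380. For two groups d = 2f = 0.4. The F test with noncentrality N·f² has power 0.899 at N = 264 and 0.901 at N = 266. Then 266 / (1 − 0.30) = 380. Both figures reproduce, so no sample-size error bears on this point.

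**2. Power of Little's test.** The protocol gives no figure, so the following are assumptions: alpha 0.05; the seven baseline outcomes entered (patient activation, physical activity, nutrition, depressive symptoms, BMI, systolic and diastolic pressure); baseline complete; follow-up missing as a block. The statistic is then approximately chi-square on p degrees of freedom, p being the number of baseline variables. Its noncentrality is N·π(1 − π)·D², where π is the proportion missing and D is the dropout-completer difference in SD on one variable (variables independent).

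N·π(1 − π) = 380 × 0.30 × 0.70 = 79.8.

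| D (SD) | Noncentrality | Power, p = 3 | Power, p = 7 | Power, p = 11 |
|---|---|---|---|---|
| 0.2 | 79.8 × 0.04 = 3.19 | 0.29 | 0.20 | 0.17 |
| 0.3 | 79.8 × 0.09 = 7.18 | 0.60 | 0.45 | 0.37 |
| 0.4 | 79.8 × 0.16 = 12.77 | 0.86 | 0.74 | 0.65 |
| 0.5 | 79.8 × 0.25 = 19.95 | 0.97 | 0.93 | 0.88 |

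With 10% missing and p = 7, power is 0.11, 0.20, 0.34 and 0.53.

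**3. Bias of the complete-case contrast.** Simulation with 2,000 trials per scenario, 190 per arm, about 30% dropout, p = 7 and no true effect. The baseline to follow-up correlation is 0.6, and the log-odds of dropout change by 0.3 to 0.8 per SD of the baseline outcome. Biases are absolute values.

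| Dropout related to baseline | Little's test rejects | Bias, unadjusted | Bias, baseline-adjusted |
|---|---|---|---|
| Same way in both arms | 44% to 100% | about 0 | about 0 |
| In one arm only | 13% to 64% | 0.06 to 0.13 SD | about 0 |
| Opposite directions by arm | 4% to 5% | 0.11 to 0.27 SD | about 0 |

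Repeating this with odds ratios of 1.5 to 2.0 per SD and correlations of 0.5 to 0.7 gave:

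- One arm only: rejection 19% to 52%, bias 0.06 to 0.14 SD.
- Opposite directions: rejection about 4% to 5%, bias 0.12 to 0.28 SD.

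Against the planning effect of d = 0.4, 0.06 to 0.14 SD is 15% to 35%, and 0.11 to 0.28 SD is 28% to 70%.

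**4. Does a non-significant test reassure?** In these scenarios it does not. At slope 0.8, the unadjusted bias among trials where the test did not reject was 0.136 SD (0.132 overall) with one-arm dropout, and 0.273 SD (0.274 overall) with opposite directions.

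**5. What imputation under MAR would not repair.** With dropout in one arm driven by the part of the follow-up value unrelated to baseline, the test rejects in about 5% of trials. The bias is then 0.07 to 0.18 SD with or without baseline adjustment.

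**The case against.** Much of the case against a stronger claim stands.

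- **Bias is not a consequence of the condition alone.** The bias figures in step 3 need baseline-related dropout that differs by arm and a model without the baseline outcome. The mechanism offered in {20a} is not arm-specific, and {11a} keeps procedure and format the same in both arms. The background does argue that patients engage more readily with lay workers, but that falls short of saying that baseline-related dropout will differ. The covariates listed for the GEE in {20a} are demographics and session frequency. The baseline outcome is not among them, though an article may not describe the model in full.
- **The test is not weak in general.** Under the stated assumptions, power is 0.74 to 0.93 for differences of 0.4 to 0.5 SD.
- **Sections {20a} and {20b} do not contradict each other merely by using different assumptions.** A sensitivity analysis is meant to vary the assumption. The argument in {20a} could even be cited as a reason why MCAR is unsupported, which would trigger imputation.
- **Imputation is not the only analysis that uses dropouts' baseline values.** A reader might infer that it is, but the primary analysis uses them too, by carrying them forward.
- **The wording is looser than a p-value rule.** The trigger is that MCAR is not supported, and no threshold is given. The attrition analysis in {20a} may also reveal differences between arms, but it yields no alternative estimate.

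None of this rescues the condition. On any reading, the opening and later sentences of {20b} disagree on whether the MAR analysis is certain to be run, and the only check named there cannot establish MCAR.

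**Conclusion.** The point holds as a weakness in a stated rule for sensitivity analysis. The MAR analysis should not depend on Little's test, because non-rejection is not evidence for MCAR and the protocol itself gives grounds to doubt it. If dropouts differ from completers by 0.2 to 0.3 SD on one variable, the present rule would trigger imputation in only about 20% to 45% of trials, under the assumptions in step 2 and with Little's test as the sole trigger.

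The possible bias of 0.06 to 0.14 SD (one arm) or 0.11 to 0.28 SD (opposite directions) is conditional on arm-specific, baseline-related dropout and no baseline adjustment. Otherwise it is about 0 when dropout depends on baseline.

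A reader might infer that the complete-case results will be biased, or that the primary result is undermined. The documents support neither: the condition affects a robustness check, not the primary estimate, and 266 and 380 are unaffected.

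**What to change.** In {20b}, delete the condition. State that multiple imputation under MAR will be run and reported for all primary and secondary outcomes whatever Little's test shows, with the baseline outcomes and the stratification variables (age, sex, education, number of chronic diseases) in the imputation model. Keep the complete-case analysis as a supplementary check; Little's test may still be reported as description. This also brings the later sentence into line with the section's opening one.

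The cost is one changed sentence and a little extra analysis, with no new data and no change in sample size. The change gives the carry-forward analysis a dependable comparator but does not test the MNAR assumption behind it. A delta-adjusted version of the imputation would explore that assumption and can be added as an option.

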### Methods in analysis to handle protocol non-adherence and any statistical methods to handle missing data {20c}

Intention-to-treat analysis will be used to minimise the impact of participant dropouts and non-adherence to the protocol by analysing all participants according to their original assignment, regardless of whether they completed the study. Missing data will be imputed using statistical methods to ensure that the analysis is not biased by missing data.

### Plans to give access to the full protocol, participant-level data, and statistical code {31c}

The full protocol will be accessible after publication. Upon reasonable request, the corresponding authors will be able to provide an anonymised dataset of participant-level data and statistical code after the main results are published.

### Oversight and monitoring

#### Composition of the coordinating centre and trial steering committee {5d}

The study team is responsible for monitoring the integrity of the study and participant safety. The study team will oversee the consent procedures, safety plans prior to the study commencement and study progress in terms of participant recruitment and retention, adverse events and protocol adherence.

#### Composition of the data monitoring committee, its role and reporting structure {21a}

The committee comprises the principal investigator, co-investigators, a project manager and a data manager. The project manager is responsible for adherence to data collection operating procedures. The data manager monitors data collection and raises queries with the project manager during data monitoring. The data manager prepares data exports for weekly review and reports to the principal investigator and co-investigators upon request.

